#### **4. Data management and statistical analysis**

##### 4.1. Data management

The staff designated by the investigator must contain the information required by the Protocol on the Data Collection Sheet (CRF).

The data of the CRF will be entered centrally by personnel designated by the Investigator through single data entry with electronic verification of data. The text elements (eg. Comments) will be verified manually. The data will be subsequently checked by the validation and control of programs listed. Obvious errors will be corrected directly from the data management staff, other errors or omissions will be verified on the medical records.

Information regarding concomitant medications will be coded using the WHO Drug Reference List, which uses the classification system Anatomic Therapeutic Chemical (ATC). Comorbidities and adverse events will be coded using the terminology of ICD9 classification.

The database will be closed once complete and accurate it said. Any change to the next data to the closure may only be made with the written agreement of the clinician responsible for the spontaneous study.

##### 4.2 Statistical methods

The aim of this study is to evaluate the efficacy of treatment with MET and CC in increasing testosterone levels in obese subjects with IGT and T2DM compared to with MET treatment and PLAC.

The data collected will be grouped and summarized with respect to demographic variables, the baseline characteristics and the efficacy and safety assessments.

The exploratory analyzes will be performed using descriptive statistics:

- Means, standard deviations, absolute and relative frequencies, range, confidence intervals.

The data will be presented for both the intent-to-treat population (ie all patients who took at least one dose of study) that for the per-protocol population (ie all patients who completed the study without major violations of protocol).

The safety assessment will be mainly based on the frequency of adverse events, including all serious adverse events. Adverse events will be summarized for each treatment group by presenting the number and percentage of patients who experienced any adverse event, an adverse event in a specific organism apparatus and a specific adverse event. Any other information collected (i.e. the severity or relationship to study drug) will be encoded as appropriate.

We will also be produced analytical lists which contain more information regarding:

- Patients who discontinued the study and the reasons therefor;
- Patients who discontinued the study due to adverse events;
- Patients who experienced serious adverse events;
- Patients with values of laboratory tests outside the predefined ranges.

Characteristics of casistica, treatments and concomitant diseases

Data on demographic and baseline characteristics and observations of efficacy and safety measures will be appropriately summarized. The characteristics of administration of the study drug and other concomitant treatments will be summarized, like the main concomitant diseases recorded on admission to the study. They will also be listed patients who discontinued the study and described in detail its reasons.

The exploratory analyzes will be performed using descriptive statistics by dividing patients by type of treatment, the treatment sequence and glucose tolerance.

Will be reported: means, standard deviations (SD), absolute and relative frequencies, range, confidence intervals.

Evaluation of effectiveness: Primary variable

The population on which will be performed the primary analysis of efficacy and 'consists of all randomized patients who have received both treatments.

The primary efficacy variable is the increase in plasma testosterone levels after treatment.

Evaluation of effectiveness: secondary variables

The secondary efficacy variables are improved metabolic control, defined by reduced levels of blood glucose and HbA1c, insulin and C-peptide, reduction of insulin resistance index (HOMA-IR), lipid improvement (reduction of levels total cholesterol, LDL and triglycerides and increased HDL levels, reduced levels of FFA), reduction of chronic inflammation (fibrinogen, CRP) and inflammatory cytokines (TNF- $\alpha$ , IL-6) after treatment.

Statistical methods (efficiency rating)

The normality of the data will be verified using of Kolmogorov-Smirnov test.

The data will be evaluated using analysis of variance (ANOVA) for repeated measures three-way (type of treatment, sequence of treatment, glucose tolerance).

Safety Rating

The population of which it will be carried out the security analysis and 'the' Safety Population 'consists of all patients included in the study who have received at least one dose of study medication.

Adverse events will be summarized by presenting the number and percentage of patients with any type of event, classified by body system and by preferred term. Other information collected (eg. Severity, causal relationship) will be penciled well as patients with serious adverse events.

Will also be listed patients had serious adverse events and discontinued the study due to adverse events.

The values of the laboratory tests will be summarized in the appropriate tables that will bring the frequency of the values outside of a predetermined range. The values that represent significant abnormalities will be listed.

Other safety data (eg. Vital signs and specific tests) will be evaluated appropriately.

### Sample size

The study was designed to demonstrate that the effect of the association of metformin and clomiphene is higher than the effect of metformin on testosterone levels after 12 weeks of treatment.

It was calculated that to have a probability of at least 80% to find, with a significance level of 5% (two-tailed), a difference between treatments of 2.8 ng / mL of testosterone level with DS of 1.5 ng / mL, a total of 20 patients (28,29) must be assessed. Therefore it was decided to randomize 24 patients in order to compensate for a drop-out rate of the order of 10-20%.

The sample size was calculated with the program "PS Power and Sample Size Calculations" of the Department of Statistics of Vanderbilt University, Nashville, TN, USA (Version 3.0.12; <http://biostat.mc.vanderbilt.edu/twiki/bin/view/Main/PowerSampleSize>) using the steps of Dupont and Plummer (28, 29).

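### The 20 patients in the sample-size paragraph do not follow from its stated inputs, which need about 6 to 8 in this crossover; the error is in the safe direction

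*Protocol*

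**What the plan says.** The paragraph headed Sample size in Protocol section 4.2 sets the aim as showing a greater effect on testosterone at 12 weeks with metformin plus clomiphene than with metformin. It fixes a two-sided 5% level, wants "to have a probability of at least 80% to find" the effect, and gives the remaining inputs and the result together as "a difference between treatments of 2.8 ng / mL of testosterone level with DS of 1.5 ng / mL, a total of 20 patients" to be assessed. It then decides to "randomize 24 patients in order to compensate for a drop-out rate of the order of 10-20" per cent.

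The paragraph names a software package but not the test. It does not say whether 1.5 ng/mL is the SD of within-patient differences or the SD of a single measurement, and it mentions no sizing by stratum. Section 3.1 makes the design a two-period crossover stratified by diabetes or impaired glucose tolerance. Section 4.2 bases the primary analysis on randomized patients who received both treatments.

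**The concern.** The stated difference is almost twice the stated SD (2.8/1.5 = 1.87). With an effect that large and each patient serving as his own control, a handful of patients reaches 80% power, so a requirement of 20 looks wrong on sight.

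This paragraph is the only justification for the number of patients. It also tells the reader which effect the trial was built to detect. Patients enter at 3 ng/mL or below (section 3.2), so a gain of 2.8 ng/mL is close to a doubling even for a man at that ceiling (5.8/3 = 1.93). A reader who takes 2.8 as the effect that 20 patients can just detect would read a null or modest result wrongly, because the trial can detect considerably less.

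**Working it through.** **Inputs** (all from the Sample size paragraph): two-sided alpha 0.05; power at least 0.80; difference D = 2.8 ng/mL; SD = 1.5 ng/mL; stated result 20 assessed, 24 randomized.

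**Formula.** With SDd the SD of the within-patient difference between treatments, the noncentrality is D / (SDd / √n). Power comes from the noncentral t with n − 1 df (simple paired test) or n − 2 df (2x2 crossover, one further df for the period effect). If 1.5 is instead a per-period SD with correlation rho between periods, SDd = 1.5 × √(2(1 − rho)), which is 2.12 at rho = 0.

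**Attempt to reproduce 20**

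| Reading | Power at the n below | Power at the smallest n that suffices | n needed |
|---|---|---|---|
| Paired t, SDd = 1.5 | n = 4: 70.2% | n = 5: 87.0% | 5 |
| Crossover, n − 2 df, SDd = 1.5 | n = 5: 78.6% | n = 6: 92.0% | 6 |
| Paired t, SDd = 2.12 | n = 6: 73.4% | n = 7: 82.7% | 7 |
| Crossover, n − 2 df, SDd = 2.12 | n = 7: 79.5% | n = 8: 87.2% | 8 |
| Parallel groups, two-sample t, SD = 1.5 | 5 per arm: 73.4% | 6 per arm: 82.9% | 12 in total |

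Worked example, second row: 2.8 / (1.5/√6) = 4.57, against a critical t of 2.78 on 4 df, gives 92.0%.

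Variants do not recover 20 either. Losing further df to the stratum factor (n − 3 or n − 4) gives 8 or 9 on the per-period reading. A correlation of −0.5 gives 9 by paired t. One-sided tests give fewer. Interchanging 2.8 and 1.5 gives 30 by paired t.

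**What 20 evaluable patients deliver**

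- Power for 2.8 ng/mL: above 99.99% with SDd = 1.5; 99.98% with SDd = 2.12; 97.6% even as 10 versus 10 parallel.
- Difference detectable at 80% power: 0.99 ng/mL with SDd = 1.5; 1.41 ng/mL with SDd = 2.12. These are 0.99/2.8 = 35% and 1.41/2.8 = 50% of the stated difference.
- Conversely, for 20 crossover patients to give exactly 80% power at 2.8 ng/mL, SDd would have to be about 4.2, or the per-period SD about 3.0 at zero correlation.

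**Drop-out.** 24 × 0.80 = 19.2 and 20/0.80 = 25, so 24 is one short at 20%. It leaves 20 evaluable up to 4/24 = 16.7%.

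**Traceability.** The paragraph cites references 28 and 29 for the method. In the reference list those are the free-testosterone and insulin-resistance papers; the sample-size papers are 32 and 33. The citations therefore do not help to recover the calculation.

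**The case against.** The strongest reply is that the paragraph asks for at least 80% power, and 20 patients meet that under every reading tested. This stands, and it rules out the most tempting inference, that the trial is underpowered. On its stated inputs it is not.

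A second reply is that N may have been set on a basis the paragraph leaves out. Section 1 plans to look at patients by glucose-tolerance state, section 3.2 fixes 12 and 12, and the ANOVA has glucose tolerance as a factor. A parallel, normal-approximation comparison inside each stratum needs 2 × (1.96 + 0.84)² × (1.5/2.8)² = 4.5, so 5 per arm, and 5 × 2 arms × 2 strata = 20 (24 with the t-test). A normal-approximation comparison of the effect between strata with SDd = 2.12 needs 10 per stratum, also 20 (11 per stratum with t). Either could be the origin. The paragraph documents neither, and the first treats a crossover as parallel groups. So this does not rescue the figure, but it does mean one cannot conclude that 2.8, 1.5 or the power must have been mistyped. Nothing in the protocol shows a transcription error.

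A reader might also infer that 24 fails its drop-out allowance. The text gives an approximate range, 24 covers most of it, and the gap is one patient at the top end. If 6 to 8 patients suffice, 19 evaluable is no shortfall for the stated effect.

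**Conclusion.** The stated 20 is contradicted by its own inputs. For the planned crossover the answer is about 6 (SD of differences 1.5) or about 8 (per-period SD 1.5, zero correlation), so the stated number is roughly two and a half to three times what those inputs require (20/8 = 2.5; 20/6 = 3.3). The defect lies in the justification of N and in the sensitivity that it conveys. Power is not too low, and the documents give no ground for changing the number randomized.

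The range depends on what 1.5 ng/mL means, which the protocol does not say. For the same reason, a flat statement that the trial can detect 1.0 ng/mL would go too far: on the per-period reading with zero correlation the figure is about 1.4. Positive correlation between periods would lower it. The drop-out wording is a minor, immaterial point.

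**What to change.** Keep 24 randomized and rewrite the paragraph:

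1. Check 2.8 and 1.5 ng/mL against their source and correct either if it is wrong.
2. Name the test and say whether 1.5 is the SD of within-patient differences or a per-period SD; if the latter, give the assumed correlation.
3. Say whether N was set overall or per glucose-tolerance stratum, and if per stratum, show that calculation for the crossover.
4. Restate what 20 evaluable patients deliver. If the inputs are confirmed, this is more than 99.9% power for 2.8 ng/mL, and 80% power for about 1.0 ng/mL (SD of differences 1.5) or about 1.4 ng/mL (per-period SD 1.5, zero correlation).
5. Point the citations to references 32 and 33. Optionally, word the drop-out allowance as up to about 16%.

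The cost is protocol wording and a check of the source figures. If the inputs are confirmed, patient numbers, visits and analysis stay as they are.

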## 5. Administrative procedures

### Good Clinical Practice standards

This study will be conducted in accordance with the principles of Good Clinical Practice (30), with the Declaration of Helsinki and national regulations regarding the conduct of clinical trials. The experimenter, by signing the Protocol, agrees to adhere to the procedures and the instructions contained therein and to conduct the study in accordance with GCP, the Declaration of Helsinki and the national regulations governing clinical trials.

### Amendments to the Protocol or any other amendments to the conduct of the study

Any changes to the protocol will be made as an amendment. Any modification to the protocol during the study period. Any unexpected change in the conduct of the trial will be recorded in "Clinical Study Report."

### Ethics committees and informed consent

The study protocol, any amendment of the protocol, informed consent and any other information for patients must be approved by the Ethics Committee of the structure where it operates the Investigator.

As regards the amendments, the investigator can immediately apply them by written notice to the Ethics Committee, without waiting for the approval of the Ethics Committee, if the safety of patients participating in the study is at stake. Also, if the investigator believes that patient safety reasons it is necessary to immediately make a change to the protocol, it must put aware the Ethics Committee of the center within 10 working days.

To participate in the study each patient will have to give written informed consent (see also section 3.2 - Study population).

### Documentation Repository

The investigator is responsible for filing and storage of essential documents of the study, before, during conducting and after the completion or termination of the study, according to the / and for the time provided by law and by GCP.

The data collected on the CRF will be strictly anonymous and the subject will be solely identified with a number and the initials.

The investigator must keep the patient's original data (eg. Demographic and medical information, laboratory data, electrocardiograms etc.) and a copy of the written informed consent signed. For some data may be established, before the beginning of the study, which are written directly on the CRF, which thus in this case will act as the original data.

### Emergency procedures for the suspension of blindness

Simultaneously sending the randomization list, which will be forwarded to hospital pharmacists identified as a reference

for the study in each experimental center and which can not be disclosed during the course of the trial to other investigators involved in the clinical trial in question, it will be forwarded to the investigator of each experimental center individual sealed envelopes corresponding to the part of the randomization list for specific experimental center. Each envelope identified with the randomisation number containing information on (drug / placebo) type of treatment given to the patient. The envelope will be sealed by the Investigator of each individual only in an emergency center. The Investigator must at the same time document the reason of the opening of the code, the date / time of the opening of the envelope and the content of the document in a sealed envelope.

The investigator shall also immediately notify the head of the study..

#### Inspection / Audits

The Investigator or delegated staff will conduct inspections during the study to ensure that it is conducted in accordance with the Protocol and the applicable regulatory requirements. Also regulatory agencies can conduct inspections on the study (during it or after the study was completed). If the Regulatory Authority requires an inspection, the investigator must immediately inform the head of the study. By signing the protocol, the investigator agrees both to audits by the study leader or deputy staff inspections of the Regulatory Authority.

#### Medication management study

The study drug will be provided entirely by the Investigator.

Metformin will be supplied as tablets of 1000 mg in packs already commercially available.

Clomiphene, supplied by the manufacturer Merck Serono as Serofene tablets of 25 mg, will be set up by the Company's Pharmacy Hospital-University of Bologna as 25 mg capsules for administration to the patient.

The investigator must ensure that the study drug is used in accordance with the protocol.

The investigator is responsible for maintaining the medication in a secure place, with limited access. The drug must be maintained in accordance with the storage conditions on the package.

#### Procedure for the preparation of the experimental sample in pharmacies

The Company's Pharmacy University Hospital of Bologna organizes experimental medicines pursuant to and in compliance with the requirements of Article 15 of Legislative Decree 06/11/2007 n. 200 in accordance with the requirements of Good Preparation Medicines, according to the current edition of the Italian Pharmacopoeia, to ensure the quality, effectiveness and safety of medicinal product prepared.

The Galenic Laboratory of Hospital Pharmacy of the Hospital of Bologna, will set the placebo capsules (rice starch) and 25 mg clomiphene.

#### **Method of preparation of capsules of 25 mg or placebo Clomiphene**

It is ground, in mortar, the tablets of Serofene from 25 mg up to obtain a fine powder.

The clomiphene powder thus obtained and possible excipients and placebo, the powder of rice starch are mixed according to the method of progressive dilutions and make it homogeneous by mixing. If they are present in a reduced quantity can be convenient to add an inert diluent excipient to increase the volume and to allow for statistically reduce the possibility of error during the subdivision.

The experimental drug or placebo will be prepared for lots with an overcoater and automatic guiding tray with 300 capsules.

The validity of the product is 6 months at room temperature with a possible option to extend it for one year on the basis of specific assessments by the trainer pharmacist.

The preparation will be documented on special register dedicated to the clinical trials on which are recorded the n. Batch, date of preparation, the quantitative composition, the validity, the discharge papers from the drug store, the signature of the preparer pharmacist, suitability for distribution of the finished product.

The capsules of experimental / placebo medication will then be packed in special polyethylene containers and labeled.

In addition, prior to deployment, the Pharmacist in charge will perform the following checks:

- Verification of the correctness of the procedures performed
- Controlling the appearance and the capsule sealing
- Monitoring the number of arranged capsules and the quantity to be dispensed
- Control of the primary and secondary packaging
- Verification of the correct label compilation
- Essay mass uniformity on the lot.

#### Publication of results

Any formal presentation or publication of data derived from this study is intended as a joint publication by the investigator and head of the study. For multi-center studies, it is mandatory that the first publication is based on the data of all the centers, analyzed according to the protocol. Investigators participating in multi-center studies agree not to submit data from a single center or a small group of centers unless there is a formal agreement by the other experimenters and [name] VA (proposer of the spontaneous study) that must receive a copy of every communication that will be published in advance of the publication itself.

#### Study Termination

The study manager reserves the right to stop the study in the case of serious adverse events associated with intake of the experimental treatment in two or more subjects recruited.

#### **Contact Persons**

The telephone and fax numbers of the contact persons for the conduct of the study are reported nell'Investigator Folder.

